**Table 2 T2:**
[figure not shown]
Secondary endpoints of the HDRACRO study.

**Table 3 T3:**
[figure not shown]
HDTACRO study design according to the SPIRIT checklist.

### Patient and public involvement

2.5

The patients and public were not involved in the planning of this study.

### Modification of the protocol

2.6

Protocol amendments will be considered by the principal investigator. All potential amendments will be submitted to the independent Ethics Committee of the University of Heidelberg for approval. No patients will be recruited until the modifications are accepted.

### Methods for minimizing bias

2.7

To avoid selection bias and heterogeneity, all patients admitted to University Hospital Heidelberg for LTx will be screened for eligibility. Every patient who meets the eligibility criteria will be informed of the study seven days after transplantation, and will be included if he/she gives consent to participate. Data will only be analyzed after all data have been collected. Any financial relationship and any conflict of interest will also be declared.

### Data management

2.8

Medical history and adverse drug reactions will be coded using the MedDRA dictionary. Medications will be coded using the WHO Drug dictionary and Anatomical Therapeutic Chemical classification. All collected data will be documented in a paper-based case report form (CRF). Data entry into CRFs at the site will be accomplished by qualified site personnel only. Entered data will be reviewed by manual reviews. Front-end edit checks will be used in addition to the manual data review to check for discrepancies and to ensure consistency and completeness of the data. After cleaning of data, a review meeting will be held to determine the occurrence of any protocol violation and to define the subject populations for the analysis. Once the database has been declared to be complete and accurate, it will be locked and the planned statistical analysis will be performed. Only authorized and well-documented updates to the study data are possible after database lock.

### Statistical design and analysis

2.9

#### Sample size

2.9.1

Since no confirmatory approach will be followed in this non-interventional study, no formal sample size estimation was carried out. For practical reasons, the number of included subjects was set to 100, which are deemed to be sufficient to provide stable estimates of the primary variable.

#### Statistical analysis

2.9.2

Dichotomous data will be presented as frequencies. Continuous data will be presented as means ± standard deviation, and in case of skewed distributions medians and ranges. To evaluate the difference between various Tacrolimus types, subgroup analysis will be performed. Accordingly, dichotomous data will be analyzed using Pearsons Chi-Squared test and continues data using repeated measure analysis of variance (ANOVA) model. A two-sided *P* value <.05 will be considered statistically significant in all analyses.

Since the amount of dose adjustments has only been partially described, the total number will be documented for each patient and evaluated as a dichotomous variable for each visit as well as a continuous variable for the time-frame between visits. Recent literature suggests that a stabilization of trough levels does not require longer than a period of 30 days for both de novo immunosuppression and conversion.^[22,23]^

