Post-transplant immunosuppressive regimens are based on a calcineurin inhibitor; either cyclosporine or tacrolimus. These medications were shown to have a similar mechanism of action through inhibition of calcineurin phosphatase.^[32,33]^ Tacrolimus acts as an immunomodulatory agent by inhibiting the transcription of the gene encoding interleukin-2 which is necessary for the T-cell-mediated immune response.^[32,33]^ The distribution of tacrolimus plays a considerable role in its metabolism. The uptake process begins in the stomach and/or proximal small bowel and the complete disintegration (and presumably optimal absorption) occurs in the distal small bowel or the colon.^[12–14]^ Therefore, this can lead to lower clearance and further increased bioavailability with the potential of toxicity.^[12–14]^ Evidence suggests that neurotoxicity, nephrotoxicity, akinetic mutism, new onset diabetes (post-transplant), gastro-intestinal toxicity, hepatotoxicity, and thrombotic microangiopathy could be associated with high levels of tacrolimus after LTx.^[34]^ As an immediate-release formulation, tacrolimus was first administered twice daily (Prograf). Two formulations of tacrolimus have been provided to be administered once daily: a prolonged-release formulation (Advagraf) and more recently an extended-release formulation (Envarsus).^[32,34–36]^ It is necessary to mention that the blood level of different types of tacrolimus should be determined and compared with each other. It is not yet clear which type is preferred. HDTACRO study is the first study to make a comparative assessment of different types of Tacrolimus. Is cannot be denied that the non-randomized selection of participants is considered as a weakness in this study.

In summary, Tacrolimus revolutionized postoperative care after LTx. Various types of this immunosuppressive drug are known, but it is not yet clear which one is preferred in terms of patient adherence and acceptance, the stability of blood level and also the rate of complications of different types of this immunosuppressive medication. The HDTACRO study will be the first study which systematically and prospectively evaluates various oral Tacrolimus-based immunosuppressives.

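### The comparison of Tacrolimus formulations names no adjustment, although formulation is chosen in clinical routine, so confounding by indication could create or mask a difference

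*Protocol article*

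**What the plan says.** The Statistical analysis section (2.9.2) states the purpose and the tools of the comparison. The purpose is "To evaluate the difference between various Tacrolimus types, subgroup analysis will be performed". The tools follow: "dichotomous data will be analyzed using Pearsons Chi-Squared test and continues data using repeated measure analysis of variance (ANOVA) model". The error rate is fixed for everything: "A two-sided *P* value <.05 will be considered statistically significant in all analyses". No covariate, stratification, matching or weighting is named there or elsewhere in the article.

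Five other places bear on this:

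- **Course of the study (2.2) and Ethics and dissemination (2.10).** Treatment is decided individually, outside the study, and follows the patient's diagnosis and clinical care. Section 2.2 also makes the early target trough depend on immune status and transplant indication, and later targets on history and indication.
- **Primary endpoint (2.4.1).** The endpoint is the number of dose adjustments needed until the individual target trough is reached.
- **Secondary endpoints (2.4.2).** Donor and recipient characteristics are to be reported. No use of them in the comparison is mentioned.
- **Methods for minimizing bias (2.7).** "To avoid selection bias and heterogeneity, all patients admitted to University Hospital Heidelberg for LTx will be screened for eligibility".
- **Abstract and Discussion.** An evident difference between therapy subgroups would lead to a randomized trial. The Discussion concedes that the "non-randomized selection of participants is considered as a weakness in this study".

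**The concern.** In a non-randomized comparison, any factor that influences both the choice of formulation and the number of dose adjustments enters the observed difference. Indication and immune status are candidates on the article's own text, because they help set the target that ends the count. If they also influence whether a patient starts Prograf or Envarsus, the planned tests compare patient mix together with formulation, and the P value cannot separate the two.

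The bias measure in section 2.7 controls who enters the study. It has no bearing on which formulation an enrolled patient receives.

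The error can go either way. A spurious difference would be published with a P value and might prompt a trial, which would then correct it. A masked difference would have no such correction, because no trial would follow.

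**Working it through.** **1. Is there a figure to reproduce?** No. On sample size the article says "For practical reasons, the number of included subjects was set to 100" and "no formal sample size estimation was carried out". It gives no effect size, SD, power or split between formulations. The point is therefore structural, and the arithmetic below only shows the scale.

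**2. The confounding path, place by place.**

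- Factor to endpoint: section 2.2 ties the target trough to indication and immune status, and section 2.4.1 ends the count of adjustments at that target. This link is in the text.
- Factor to formulation: sections 2.2 and 2.10 say treatment is individual and follows diagnosis. They do not say how Prograf or Envarsus is chosen. This link is plausible but not documented.
- Adjustment: Pearson chi-squared cannot carry a covariate. Section 2.9.2 evaluates dose adjustment as a dichotomous variable at each visit, so one stated form of the primary variable goes through that test. Repeated-measures ANOVA could carry covariates, but none is named.

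**3. Illustration: false positives.** From the document: total of 100, two-sided alpha of 0.05. Assumed: a 50:50 split, residual SD 2.5 adjustments, no true formulation effect, and one binary prognostic factor worth b adjustments with prevalence p1 and p2 in the two groups (p1 + p2 = 1).

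- Spurious difference: d = b × (p2 − p1)
- Variance per group: v = 2.5² + b² × p1 × (1 − p1)
- Standard error: SE = √(2v/50)
- Rejection rate: Φ(d/SE − 1.96) + Φ(−d/SE − 1.96)

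| b | p1 vs p2 | d | v | SE | d/SE | Rejection rate | Simulated (5,000 runs, t-test) |
|---|---|---|---|---|---|---|---|
| 2 | 30% vs 70% | 0.8 | 7.09 | 0.533 | 1.50 | 32% | 31.2% |
| 2 | 40% vs 60% | 0.4 | 7.21 | 0.537 | 0.74 | 12% | 11.6% |
| 1 | 30% vs 70% | 0.4 | 6.46 | 0.508 | 0.79 | 12% | 12.6% |
| 1 | 40% vs 60% | 0.2 | 6.49 | 0.510 | 0.39 | 7% | 7.4% |

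**4. Illustration: masking.** Units are the within-stratum SD. Assume a true difference of 0.6, 50 per group, and a factor worth 1.0 that acts in the opposite direction.

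- No imbalance: v = 1 + 0.25 = 1.25, SE = 0.224, 0.6/0.224 = 2.68, power about 77%.
- 20-point imbalance: observed difference 0.6 − 0.2 = 0.4, SE = 0.223, ratio 1.80, power about 44%.
- 40-point imbalance: observed difference 0.6 − 0.4 = 0.2, SE = 0.220, ratio 0.91, power about 15%.

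**5. Does adjustment help?** A separate simulation used 4,000 trials per setting, 50 per group, imbalances of 20 to 60 points and factor effects of 0.5 or 1.0 SD. The unadjusted false-positive rate ran from about 8% to 78%. With the factor in a linear model it was 4.4% to 5.2%. That holds for a factor that is measured and correctly modelled.

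**The case against.** The best defence is that this is a pilot, exploratory, non-interventional study with no confirmatory claim. Its stated aim is to describe trough levels and the need for dose adaptation, the comparison is called a subgroup analysis, and the Discussion admits the lack of randomization. Covariates may also be listed in a full protocol or analysis plan that is not shown. This lowers the weight of the point but does not remove it. The article itself names the tests and the significance threshold for this comparison, presents the study as a comparative assessment of formulations, and links a subgroup difference to a further trial. Admitting a weakness does not make the contrast interpretable.

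Four stronger readings are tempting, and the document does not support them:

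- **That the comparison is shown to be biased.** The article does not say how formulation is chosen, so neither the presence nor the direction of confounding is established.
- **That a P value formally decides whether a trial follows.** The wording is loose and sets no numerical trigger.
- **That the analysis populations are open to manipulation.** Section 2.8 says "a review meeting will be held to determine the occurrence of any protocol violation and to define the subject populations for the analysis", and this takes place before database lock. That is ordinary practice and a separate matter from confounding.
- **That every useful covariate is already collected.** Tables 2 and 3 are not visible here, and the readable text does not list immune status or the day of first oral dose as recorded variables.

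**Conclusion.** The point holds as a weakness in the analysis as the article states it. For a comparison of clinician-chosen formulations, section 2.9.2 names tests and a significance threshold but no adjustment, while the endpoint depends on a target set by patient factors. Confounding by indication is plausible, of unknown size and direction, and could create or conceal the subgroup difference. Screening all admissions does not reduce it.

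The figures of about 7% to 32% for false positives, and the loss of power from about 77% to 44% or 15%, are illustrations. The split, SD, factor effect and imbalance are all assumed, and the calculation uses a simple two-group comparison of one count, not the planned repeated-measures model. They show that moderate imbalance would matter at this sample size, not that it will occur.

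**What to change.** Amend section 2.9.2 for the between-formulation comparison, before any outcome is analysed by formulation:

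- Prespecify a short list of confounders fixed before treatment and drawn from the recorded donor and recipient characteristics. Examples are recipient age, body weight, indication, baseline renal function and the initial target set before the first oral dose, each only where it is recorded. Leave out later targets, since they may be affected by treatment.
- Make a regression-adjusted or propensity-weighted estimate with a 95% confidence interval the main contrast, and show the unadjusted result beside it.
- Classify each patient by the first oral formulation started.
- Label the P values as exploratory, and state that unmeasured confounding remains.

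The cost is analysis wording, some analyst time and possibly wider intervals where the groups overlap poorly. No extra patients are needed. Whether each covariate is available must be checked against the case report form.

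The list has to be fixed in advance, because covariates chosen after the results are seen would not be credible.

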### Course of the study

2.2

As shown in Table 3, the treatment and patient care will follow standard clinical practice for liver transplant patients at the Department of General, Visceral and Transplantation Surgery, University Hospital Heidelberg. The individual treatment decision will be taken independently from the participation in this non-interventional study. For all patients a total of 8 visits, as part of clinical routine, is planned from visit 1/day 0 until visit 8/day 180 (end of study) (Table 3). All data until visit 5 (day 7) will retrospectively be observed via clinical IT-System i.s.h.med of the University Hospital Heidelberg. On the fifths patient visit (post-operative day 7), the informed consent will be obtained from all participants. From this time point on, all data will be observed prospectively and documented (Table 3). Similar to the clinical routine, as soon as a patient is able to swallow and has a sufficient gastrointestinal activity, Tacrolimus-based immunosuppression using Prograf, or Envarsus will be started. Furthermore, CNI-based immunosuppression will be used (initial dose based on the patients body weight) with the goal of trough levels of 3 to 7 ng/ml within the first seven days after LTx, depending on immune status and indication for transplantation. Further trough levels will be determined based on factors such as patients history and indication for LTx. To minimize renal and infectious complications, a “bottom-up” dosing procedure (as a concept of delayed CNI-based immunosuppression) will be routinely used.

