#### Secondary endpoints

2.4.2

As presented in Table 2, demographics and clinical characteristics of donors and recipients will be reported. Tacrolimus related information including: Tacrolimus trough level, Tacrolimus dosing, concentration/dose ratio, mean cumulative dose for cost analysis, will be recorded during patient visits. Furthermore, routine laboratory tests will be assessed and reported for each patient. Finally, efficacy data (incl. survival, acute rejection, re-transplantation), patients therapy adherence, and infections requiring the need to reduce individual Immunosuppressant dosing will be evaluated for each patient. Afterwards, the number of patients who require a change in immunosuppressive therapy, the stability of Tacrolimus trough levels and effectiveness of delayed CNI-based immunosuppression with Tacrolimus will be determined and the renal and transplant function under delayed CNI-based immunosuppression with Tacrolimus will be assessed.

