### Ethics and dissemination

2.10

The independent Ethics Committee of the University of Heidelberg has approved the protocol of present study (registration number: S-630/18). This study was designed in accordance with the Declaration of Helsinki, version 2013. Participation will be voluntary and consent may be withdrawn at any time, without explanation and with no impact on further medical care. The execution of the trial is carried out in the Department of General, Visceral and Transplantation Surgery of the University Hospital Heidelberg. According to paragraph 4 Abs. 23 AMG the medical treatment of the patients will be undertaken based on their diagnosis and clinical treatment and not based on this protocol. The results of this study will be published in a peer-reviewed journal, and will also be presented at medical meetings.

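### Repeated-measures ANOVA is a poor fit for tacrolimus data with delayed start, unequal visit spacing and loss before day 180; a likelihood-based mixed model should replace it

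*Protocol article*

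**What the plan says.** The Statistical analysis section (2.9.2) introduces testing for one purpose: "To evaluate the difference between various Tacrolimus types, subgroup analysis will be performed". It then fixes the methods: "dichotomous data will be analyzed using Pearsons Chi-Squared test and continues data using repeated measure analysis of variance (ANOVA) model". Significance is judged throughout at the two-sided 0.05 level. No other test is named. The same section treats the number of dose adjustments between visits as continuous, so a comparison of formulations on the primary variable would use the ANOVA too.

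The data are longitudinal. Under Secondary endpoints (2.4.2), "Tacrolimus trough level, Tacrolimus dosing, concentration/dose ratio, mean cumulative dose for cost analysis, will be recorded during patient visits". Under Course of the study (2.2), "a total of 8 visits, as part of clinical routine, is planned from visit 1/day 0 until visit 8/day 180". Visit 5 is day 7, so five visits lie in the first week and three in the remaining 173 days. Data up to visit 5 are taken retrospectively from the hospital system, and consent is sought on day 7. Tacrolimus begins only when the patient can take it by mouth and the gut is working, within a deliberately delayed approach. Under Ethics and dissemination (2.10), "consent may be withdrawn at any time".

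On size, "the number of included subjects was set to 100" and "no formal sample size estimation was carried out".

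**The concern.** Classical repeated-measures ANOVA makes two demands that this design is unlikely to meet.

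- **Complete rows.** A patient lacking any visit in the analysed set contributes nothing. Before the first dose there is no meaningful trough, and the concentration/dose ratio has a zero denominator. These early gaps are built in and depend on how fast the patient recovers. Later gaps come from death and withdrawal.
- **Sphericity.** The tests of visit and of formulation-by-visit assume that differences between any two visits have equal variance. Visits a day or so apart in week one are unlikely to relate to each other as visits months apart do.

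The comparison could therefore rest on patients who started early and survived. That would affect the estimates as well as the P values. It matters even in an exploratory study, because the Conclusion of the abstract and the end of the Discussion make an evident difference between therapy subgroups the reason to design a randomized trial.

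**Working it through.** The plan's own figure, 100 patients, has no effect size, standard deviation or power behind it, so there is nothing to reproduce. The checks below ask how much a complete-row analysis could lose, and whether the chi-squared part is a problem of the same kind.

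**1. Deaths by day 180.** Input: 83% one-year survival, a background figure in the Discussion and not a forecast for this cohort. Assumption: constant hazard.

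- From day 0: 1 − 0.83^(180/365) = 0.088, about 8.8%.
- Patients consent on day 7, so those enrolled have survived to then. From day 7: 1 − 0.83^(173/365) = 0.085, about 8.5%.
- Without the constant-hazard assumption, the same source figure caps the loss at 17%, if every first-year death came before day 180.

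**2. Share of patients with complete rows.** Assumption: each visit is missing independently with probability m. The article gives no rate. Share kept = (1 − m)^k, with k = 3 (visits 6 to 8) or k = 8 (all visits).

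| m | k = 3 | k = 8 |
|---|---|---|
| 1% | 97% | 92% |
| 2% | 94% | 85% |
| 5% | 86% | 66% |
| 10% | 73% | 43% |

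Independence is the pessimistic case. If the same patients missed every visit, the share kept would be 1 − m: 98% at m = 2% and 95% at m = 5%. In the other direction, for trough and concentration/dose ratio the k = 8 column may be too kind. Any patient not yet on tacrolimus at visit 1 (day 0) has no value there and so cannot have a complete eight-visit row. The article does not say how many patients that is.

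**3. Covariance.** The uniform-correlation structure behind classical ANOVA has 2 parameters (one variance, one correlation). An unstructured matrix over 8 visits has 8 × 9 / 2 = 36. Structures in which correlation falls with elapsed time lie between.

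**4. Pearson chi-squared with few events.** Assumptions: event rates of 2% to 25% and splits of 50/50, 70/30, 80/20 and 90/10, as the article gives neither. At 8.8% the smallest expected cell is 50 × 0.088 = 4.4 (50/50) or 20 × 0.088 = 1.8 (80/20), below the usual threshold of 5. The true type I error was found by summing the two-binomial probabilities of all tables rejected at 0.05, over 28 scenarios:

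- At 8.5% events: 0.048 (50/50), 0.048 (70/30), 0.035 (80/20), 0.050 (90/10).
- Clear inflation only at 80/20 with 2% or 3% events: 0.087 and 0.072. The other 26 scenarios lie between 0.013 and 0.054.
- Fisher's exact test: 0.0004 to 0.035, more conservative than Pearson in every scenario.

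**5. Follow-up time.** A patient who withdraws event-free before day 180 has no 180-day outcome. Pearson's test must either count that patient as event-free to day 180 or leave the patient out. Neither uses the time actually observed.

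**The case against.** The strongest reply is that the article names an ANOVA model and stops there. It states no deletion rule, covariance structure or missing-data method. Such details commonly sit in the full protocol or analysis plan, which is not shown. This stands in part. A reader might infer that patients with a missing visit will be dropped, but the text does not say so, and the wording could loosely mean a mixed model. What remains is that a method has been named, and in its ordinary sense it suits these data badly.

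Second, visits 1 to 5 come from existing records and consent is given on day 7, so loss to follow-up falls on visits 6 to 8. That is right for documentation, and the three-visit figures are the fairer ones for laboratory values. It does not help with troughs and ratios that never existed because the drug had not been started.

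Third, a reader might infer from the small expected counts that Pearson's test is invalid and that Fisher's is required. The exact calculation does not support this. Pearson's size is near or below 0.05 in most scenarios, and Fisher's test gives up power, so the choice is a trade-off. A reader might also infer that survival will be tested by chi-squared. The article assigns no test to survival, and its tests concern comparisons between formulations, not every outcome.

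Fourth, a mixed model is no complete cure. It assumes missing at random, it does not give meaning to values before first dose or after death, and early visits will still contain only those already on treatment. All of this is true, and is a reason to state the assumptions. Complete-row ANOVA has the same limits and discards data as well.

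Last, the study is exploratory. That lowers the weight of the point but does not remove it, since the comparison is meant to inform a trial.

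**Conclusion.** The point holds for continuous repeated measures compared between formulations. The named method, in its classical form, needs complete rows and sphericity, and delayed start, uneven visit spacing, death and withdrawal make both unlikely. If complete rows were required, 6% to 14% of patients would be lost over visits 6 to 8, and 15% to 34% over all 8, at 2% to 5% missing per visit. Those rates and their independence are assumptions. The 8.8% mortality by day 180 rests on the article's background survival and a constant hazard. The direction of selection, towards early starters who survive, does not depend on these figures.

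For survival, rejection and re-transplantation the conclusion is conditional. If they are compared between formulations, the reason not to use Pearson's test is that it ignores follow-up time. Small cells are a minor matter. The change should be made before the analysis, but it is not a flaw that invalidates an exploratory study.

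**What to change.** In the Statistical analysis section, replace the repeated-measures ANOVA by a likelihood-based mixed model for repeated measures that uses all available values after tacrolimus start. Include formulation, visit and formulation-by-visit, with a covariance structure that allows for unequal visit spacing. With 100 patients, a structure based on elapsed time or with heterogeneous variances is a sensible fallback if the 36-parameter unstructured form does not converge. State that values before the first dose are undefined rather than missing, and that later gaps are assumed missing at random.

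Add that any comparison of survival, acute rejection or re-transplantation between formulations will use Kaplan-Meier or cumulative incidence estimates with 95% confidence intervals. Pearson's test can stay for dichotomous data without a follow-up-time element.

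The cost is a change of wording. It needs no new data, visits or patients, and standard software suffices. The price is reliance on missing at random and a few more parameters. If a mixed model was already meant, the change only makes that explicit.

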The development of once-daily Tacrolimus formulations has already been shown to increase patients adherence.^[14,15]^ Although, it has slightly influenced the Tacrolimus pharmacokinetic profile, while the dissolving form still remains intact.^[14,15]^ The pharmacokinetic profile of once-daily Tacrolimus is characterized by flatter kinetics (i.e., less fluctuation and swing) compared to a twice-daily regimen. Thus, once-daily Tacrolimus can also lead to reduced incidence and/or intensity of drug toxicity-related adverse events, by providing a more balanced concentration-time consistency over 24 hours. Since the development of LCP-Tacrolimus once-daily tablets, using the MeltDose technology, clinical data have shown lower peak and reduced peak-to-trough fluctuations.,^[16,17]^ as well as an improved clinical safety profile.^[18]^ Furthermore, trials with stable kidney or liver transplant recipients who were switched from twice-daily Tacrolimus capsules to once-daily LCP-Tacrolimus tablets showed a similar area under the concentration–time profile (AUC24) with reduced doses of LCP-Tacrolimus.^[19–21]^

The aim of the present study is to assess the trough levels and the need for adaptation of therapeutic doses in de novo LTx patients treated with Tacrolimus in the clinical routine, without any intervention to the treatment regimen.

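### The formulation comparison rests on an ANOVA that in its standard form pools variance, while stability is a study question and the group split is left to routine care; if groups prove unequal in size and spread, the 5% level will not hold

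*Protocol article*

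**What the plan says.** Section 2.9.2 (Statistical analysis) sets out the comparison of formulations: "To evaluate the difference between various Tacrolimus types, subgroup analysis will be performed". Dichotomous data go to a chi-squared test and "continues data using repeated measure analysis of variance (ANOVA) model". The threshold is general: a two-sided P "value <.05 will be considered statistically significant in all analyses". No variance option, correction or alternative test is named. Dose adjustments, the primary endpoint, are also to be treated as continuous for the intervals between visits, so they fall under the same method.

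Three other places bear on whether equal variances are a sensible default.

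- Section 2.4.2 (Secondary endpoints) lists "the stability of Tacrolimus trough levels" among the things to be determined. The Discussion treats stability of blood level as one of the respects in which it is still unclear which formulation is preferable.
- The Introduction says that once-daily Tacrolimus has "flatter kinetics (i.e., less fluctuation and swing) compared to a twice-daily regimen".
- Section 2.2 (Course of the study) leaves the choice of product to clinicians: "The individual treatment decision will be taken independently from the participation in this non-interventional study". Section 2.9.1 fixes only a total: "the number of included subjects was set to 100". There is no target per formulation.

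**The concern.** In a standard repeated-measures ANOVA with two groups, the test of the group effect is the pooled-variance two-sample test on patient means. The group-by-visit test likewise pools the within-patient variance over both groups. Pooling does little harm when the groups are of equal size. When they are not, the common variance is dominated by the larger group. If the smaller group is the more variable one, the standard error is too small and false positives rise. If the larger group is the more variable one, the standard error is too large and real differences are missed.

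Here the study itself asks about the stability of levels, and nothing in the design keeps the groups balanced. The abstract and the Discussion say that a randomized trial would be designed if a difference between the therapy subgroups is evident. A comparison that flags too often or too rarely is a poor guide to that step, and its intervals would mislead whoever plans the next trial.

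**Working it through.** **Inputs from the documents.** N = 100 in total (2.9.1); two-sided 5% (2.9.2); 8 visits from day 0 to day 180 (2.2); two formulations.

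**Assumed inputs, not in the documents.** Splits from 50/50 to 20/80; SD ratios between formulations of 1.25 to 2; normal data; equal true means.

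**The plan's own figure.** With equal SDs, simulation of the pooled test (98 degrees of freedom) gives 4.9 to 5.1% at every split. The stated 5% is reproduced when variances are equal.

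**Formulas for the group test.** Let n₁, n₂ be the group sizes and s₁, s₂ the SDs of patient means.

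- Variance that the pooled test uses, on average: [(n₁−1)s₁² + (n₂−1)s₂²]/98 × (1/n₁ + 1/n₂)
- True variance of the difference: s₁²/n₁ + s₂²/n₂

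**25/75, smaller group with SD 2, larger with SD 1.**

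- Pooled: (24×4 + 74×1)/98 = 1.735; × (1/25 + 1/75) = 0.0925
- True: 4/25 + 1/75 = 0.1733
- The critical value 1.984 acts like 1.984 × √(0.0925/0.1733) = 1.450. The normal tail gives 14.7%; simulation, which also allows for estimating the variance, gives 15.2%.

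**25/75, larger group with SD 2.**

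- Pooled: (24×1 + 74×4)/98 = 3.265; × 0.0533 = 0.1741
- True: 1/25 + 4/75 = 0.0933
- The critical value acts like 1.984 × √(0.1741/0.0933) = 2.711. The normal tail gives 0.7%; simulation gives 0.8%.

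**Range.** Simulated level of the nominal 5% group test, smaller group more variable / larger group more variable:

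| Split | SD ratio 1.25 | SD ratio 1.5 | SD ratio 2 |
|---|---|---|---|
| 50/50 | 5.0% | 5.0–5.1% | 5.0–5.1% |
| 40/60 | 6.1% / 4.1% | 7.0% / 3.5% | 8.3% / 2.8% |
| 35/65 | 6.6% / 3.6% | 8.1% / 2.8% | 10.4% / 1.9% |
| 25/75 | 7.9% / 2.9% | 10.7% / 1.8% | 15.2% / 0.8% |
| 20/80 | 8.6% / 2.6% | 12.2% / 1.4% | 18.0% / 0.5% |

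Welch's test stayed at about 5% in every cell.

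**If only within-patient SD differs.** Stability over time is mainly within-patient variation, so this case is closest to the study's question. Assume between-patient SD 1 in both groups, within-patient SD 1 in one and 2 in the other, 8 visits with compound symmetry, and a 25/75 split.

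- Variance of a patient mean: 1 + 1/8 = 1.125 against 1 + 4/8 = 1.5. The SD ratio of patient means is √(1.5/1.125) = 1.15, not 2.
- Group test: 6.8% / 3.6% when simulated on patient means, 7.3% / 3.7% in a full repeated-measures simulation with 6,000 runs.
- Group-by-visit test: the within-patient variance ratio is still 4, so the mean square is inflated by 0.1733/0.0925 = 1.87 or shrunk by 0.0933/0.1741 = 0.54. Against the critical F of 2.02 on 7 and 686 degrees of freedom, a chi-squared approximation gives 37% and 0.04%. Simulation gives 38.4% and 0.1%.
- At 50/50 both tests stay at about 5%.

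**Price of Welch when variances are equal.** The simulated power loss against the pooled test was nil at 50/50, up to 0.4 points at 35/65, up to 1.2 points at 25/75 and up to 2.1 points at 20/80, over standardized differences of 0.3 to 0.8.

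**The case against.** Several points on the other side are fair.

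- **The article never says equal variances.** It names a model family, and a full analysis plan that is not shown might add group-specific variances. That is possible. Still, the method is stated rather than left open, and its standard form pools.
- **Split and SD ratio are assumptions.** A reader might infer that the 5% level is in truth about 15% or below 1%. The documents do not support that: this pair needs roughly 25/75 and an SD ratio of 2, and neither figure appears anywhere. Nor do they show that the groups will be unequal; they show only that nothing makes them equal.
- **The fluctuation argument is indirect.** The Introduction's remark on flatter kinetics concerns the 24-hour profile. It does not imply that patient means of trough levels, or numbers of dose adjustments, have a larger SD under one product. Under the within-patient difference that the stability question does suggest, the group test is only mildly off, and the large distortion is in the group-by-visit test.
- **The study is exploratory.** Section 2.9.1 says: "Since no confirmatory approach will be followed in this non-interventional study, no formal sample size estimation was carried out". A reader might conclude that the 5% rule fails as an error guarantee, but no such guarantee is claimed. Nor is the later randomized trial tied to P<.05; the text speaks only of an evident difference.
- **A richer model has its own cost.** An unstructured covariance matrix for 8 visits has 8×9/2 = 36 parameters per formulation, and 25 patients would be too few to estimate it well. This rules out that version of the remedy, not the remedy itself.

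What stands is that a pooled test is a poor default where spread may differ and group sizes are uncontrolled, and that a better one is easily available.

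**Conclusion.** The point holds in conditional form. As written, the formulation comparison keeps its 5% level if the variances are equal, and nearly so if the groups are balanced. Away from that, the group test drifts from slightly off (6.1% / 4.1% at 40/60 with an SD ratio of 1.25) to clearly off (15.2% / 0.8% at 25/75 with a ratio of 2). The group-by-visit test can be far worse (about 38% / 0.1%) when only within-patient SD doubles at 25/75. All of these rest on assumed splits and SD ratios, normal data and, for the repeated-measures figures, compound symmetry.

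In an exploratory pilot this is a worthwhile improvement to a screening test. It does not invalidate the study, and correcting it leaves untouched the confounding from non-randomized choice of formulation, which the Discussion itself acknowledges as a weakness.

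**What to change.** In 2.9.2, state that comparisons between formulations will not assume equal variances:

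- **Patient-level summaries and once-only measures:** Welch's test.
- **Repeated measures:** a mixed model with formulation-specific variance parameters in a parsimonious covariance structure (for example, separate between- and within-patient variances per formulation under compound symmetry), with Satterthwaite or Kenward-Roger degrees of freedom. Do not use a fully unstructured matrix per formulation.
- **Reporting:** the number of patients, SD and confidence interval for each formulation. The SDs also describe stability directly.

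The cost is a sentence or two and standard software options, with no change to treatment, visits or data collection. For Welch the loss is about 0 to 2 percentage points of power if the variances turn out equal. The mixed model was not simulated here, so its small-sample behaviour should be checked at the observed group sizes.
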